### Outcome measures and calculation algorithms

#### Primary outcome.

The primary outcomes will include three time-domain indicators and two frequency-domain indicators calculated through software analysis, along with the symmetry index (SI), muscle activation sequences, and muscle contribution ratios derived from these indicators.

(1)The time-domain indicators will include root mean square amplitude (RMS), integral electromyography (IEMG), and average electromyography (AEMG), which are primarily related to muscle contraction force. The formulas for these calculations are as follows:

$$\begin{array}{c} RMS\;=\;\sqrt{\frac{\sum {\mathrm{\backslash nolimits}}_{i=0}^{N}Data{\left[i\right]}^{2}}{N}} \end{array}$$

$$\begin{array}{c} IEMG\;=\;\sum_{i=0}^{N}\left|Data[i]\right|\times \Delta t \end{array}$$

$$AEMG=\frac{1}{N}\sum_{i=1}^{N}\left|xi\right|$$

In the aforementioned formulas, Data[i]denotes the EMG signal value at the i-th sampling point. Nrefers to the total number of sampling points, which represents the number of data points collected over a specific time period. iis the index indicating the position of the data point, ranging from the first to the N-th. Δtrepresents the time interval between consecutive sampling points. xi denotes the absolute value of the EMG signal at the i-th sampling point.

(2)The frequency-domain indicators will include mean power frequency (MPF) and median frequency (MF), commonly used to assess muscle fatigue.

$$MPF=\frac{\sum {\mathrm{\backslash nolimits}}_{i=1}^{N}f_{i}\cdot P_{i}}{\sum {\mathrm{\backslash nolimits}}_{i=1}^{N}P_{i}}$$

MF=Median(f(P(f)))

In the aforementioned formulas, $f_{i}$represents the i-th frequency point, while $P_{i}$corresponds to the power spectral density value at the i-th frequency point. Nis the total number of frequency points. P(f)is the power spectral density as a function of frequency f, and frefers to the frequency point.

(3)SI: The formula for calculating SI in this study will be SI = (left RMS – right RMS)/ (left RMS + right RMS). A result greater than 0 will indicate that the discharge from the muscles on the left side is greater than that on the right, and a result less than 0 will indicate the opposite.(4)Muscle activation sequences: When the average of 10 consecutive sampling points of the EMG signal first exceeds the baseline value (where the baseline is defined as 1.7 times the maximum value of the first 20 sampling points), that time point is recorded as the muscle activation onset time. Subsequently, when the average of 10 consecutive sampling points falls below the baseline, that time point is recorded as the muscle activation offset time. By sorting the activation onset times of each muscle, the muscle that activates earliest is ranked first, determining the muscle activation sequence.(5)Muscle contribution rate: This rate will be defined as the percentage of the IEMG values of each test muscle relative to the total IEMG values of all test muscles across the five analyzed gait cycles [25]. This measure will reflect the extent of muscle involvement during the walking process.

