### Primary and secondary objectives

The primary objective of this study is to compare the surface electromyography (sEMG) signal parameters of the rectus femoris, semitendinosus, tibialis anterior, and medial head of the gastrocnemius muscles in both lower extremities during a 10-meter walk test between frail and non-frail older adults in order to characterize changes in lower extremity sEMG signals in frail older adults.

Secondary objectives are to explore the correlations between EMG parameters and frailty states and to assess the predictive validity and diagnostic value of EMG parameters for frailty states.

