### Sample size calculation

The sample size calculation was performed using G*Power 3.1.9.7, based on an effect size of 0.433 derived from pilot study data. With a power of 80% and an alpha level of 0.05, the required sample size was calculated to be 67 subjects per group. Anticipating a 10% attrition rate, the sample size was adjusted to 75 subjects per group, resulting in a total of 150 subjects to ensure adequate power for detecting significant differences.

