### Muscles to be tested

Based on the relevant literature and preliminary data analysis, the muscles selected for testing in this study are the rectus femoris, semitendinosus, tibialis anterior, and the medial head of the gastrocnemius in both lower limbs of older adult participants.

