### Statistical analysis

Statistical analysis will be conducted using SPSS 24.0 software, with graphical representations generated through Graph Pad Prism 8. Measurement data will be analyzed by the Kolmogorov-Smirnov test (K-S test), expressed as mean ± standard deviation (x̅ ± s) if they adhere to a normal distribution, with comparisons between groups made using the two independent samples t-test. For non-normally distributed data, results will be described using the median (interquartile range) [M(IQR)], and comparisons between groups will be conducted using the Mann-Whitney U test. Count data will be expressed as frequency (n) and constitutive ratio (%), with comparisons between groups performed using the χ^2^ test or Fisher’s exact test, and rank data comparisons utilizing the Wilcoxon rank-sum test. Effect sizes will be calculated using Cohen’s d value, and the significance level will be set at a two-sided *P *< 0.05.

The intraclass correlation coefficient (ICC) analysis, specifically the ICC(3,k) model, will be used to quantify the consistency and reproducibility of measurements. To assess the reliability of single measurements, the standard error of measurement (SEM) will be calculated using the formula SEM = SD/$\sqrt{n}$, where n represents the number of measurements per participant (i.e., 3). Additionally, the minimum detectable difference (MDD) will be calculated using the formula MDD = SEM × 1.96×$\sqrt{2}$ to determine whether observed differences exceed those expected from measurement error alone, at the 95% confidence level.

Associations between sEMG parameters and frailty status will initially be assessed using Pearson correlation analysis for normally distributed data or Spearman rank correlation analysis for non-normally distributed data. Subsequently, EMG parameters significantly associated with frailty status will be included in binary logistic regression models to further assess their predictive ability for frailty status, controlling for potential confounders such as age and gender. Finally, EMG parameters that prove significant in the logistic regression analysis will be evaluated for their sensitivity, specificity, and cutoff values for diagnosing frailty using receiver operating characteristic (ROC) curves.

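### Eight unranked primary sEMG parameter types, measured on four muscles in both limbs, share one two-sided 0.05 level, while the sample size rests on a single effect tied to no named parameter

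*Protocol article*

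**What the plan says.** The Primary outcome section of the protocol article opens: "The primary outcomes will include three time-domain indicators and two frequency-domain indicators calculated through software analysis, along with the symmetry index (SI"). The same sentence goes on to include "muscle activation sequences, and muscle contribution ratios derived from these indicators". The Abstract lists the same eight types: RMS, IEMG, AEMG, MPF, MF, SI, activation sequence and contribution rate. Neither place puts one of them first.

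The primary objective applies these to the "rectus femoris, semitendinosus, tibialis anterior, and medial head of the gastrocnemius muscles in both lower extremities during a 10-meter walk test", which is eight recording sites. Under Statistical analysis, "the significance level will be set at a two-sided" P < 0.05, and this one level serves every comparison. The section Sample size calculation is "based on an effect size of 0.433 derived from pilot study data", with 80% power, alpha 0.05 and 67 per group, raised to 75 for 10% attrition. It does not say which parameter or muscle gave 0.433, or whether alpha is one- or two-sided.

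**The concern.** With an unranked primary family and one level per test, any one of many comparisons can be reported as a positive primary result. The error rate of the overall conclusion, that frail adults have a characteristic sEMG profile, is then not controlled.

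The effect carries forward. The Statistical analysis section takes parameters significantly associated with frailty status into logistic regression, and those significant there into ROC cutoffs, all in the same participants. With a two-group status, a Pearson correlation test is the two-sample t-test in another form. A chance hit in the group comparison is therefore also a chance hit in the screening step, and can end as a diagnostic cutoff.

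Several parameters also measure nearly the same thing, so one chance signal can look like several agreeing findings. Finally, the power claim concerns one effect, and a reader cannot tell which primary outcome it covers.

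**Working it through.** **1. The plan's own figure.** Inputs from Sample size calculation: effect 0.433 (taken as Cohen's d, an assumption), power 80%, alpha 0.05, equal groups. For the two-sample t-test the noncentrality is d × √(n/2).
- At n = 67: 0.433 × √33.5 = 2.51. Noncentral-t power is 80.2% one-sided and 70.1% two-sided.
- At n = 75: 0.433 × √37.5 = 2.65. Two-sided power is 75.0%.
- The smallest n reaching 80% is 67 per group one-sided and 85 two-sided.
- Attrition: 67 / 0.9 = 74.4, so 75, as stated. For 85: 85 / 0.9 = 94.4, so 95.

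The figure of 67 is thus reproduced exactly, but only with a one-sided test, whereas the analysis is two-sided.

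**2. Number of primary comparisons.** The article gives none, so this is a reader's count under stated assumptions.
- Each muscle and side tested separately: 5 indicators × 8 sites = 40. SI, defined as "SI = (left RMS – right RMS)/ (left RMS + right RMS"), adds one per muscle pair, 4. Onset ranks add 8. Contribution rate, the "percentage of the IEMG values of each test muscle relative to the total IEMG values of all test muscles", adds 8. Total 40 + 4 + 8 + 8 = 60.
- Limbs averaged: 5 × 4 + 4 + 4 + 4 = 32.
- One test per parameter type: 8.

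**3. Expected false positives if nothing differs** (0.05 × k, whatever the correlation): 0.4 for 8, 1.6 for 32, 3.0 for 60.

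**4. Chance of at least one, independent tests** (1 − 0.95^k):
- k = 8: 33.7%
- k = 32: 80.6%
- k = 60: 95.4%

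**5. Allowing for correlation.** The outcomes are linked by definition. IEMG is the summed absolute signal times Δt, and AEMG is that sum divided by N, so IEMG = AEMG × duration, up to indexing. MPF and MF summarise one spectrum. SI comes from RMS, and contribution rates come from IEMG and sum to 100%. The article gives no correlations, so the values below are assumed and the test statistics were simulated under no difference.
- 60 tests, correlation 0.90-0.98 within the amplitude measures and within the frequency measures of a muscle, 0.3-0.8 between muscles: 87% falling to 69%. The 40 site-level tests alone, same settings: 67% falling to 32%.
- 60 tests, one common correlation among all: 85% (0.3), 67% (0.5), 43% (0.7), 20% (0.9).

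Correlated versions of the 8- and 32-test counts were not run; they would lie below the independence figures in step 4.

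**6. Power if all stayed co-primary.** As an illustration only, Bonferroni at two-sided 0.05/k with d = 0.433 gives 45% power at 75 per group for 8 tests and 23% for 60. Reaching 80% would take 139 and 190 per group, or 155 and 212 with attrition.

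**The case against.** A reader might infer that at least one false primary finding is close to certain. The document does not support that. It would need about 60 tests that are independent and all truly null. The article never says that each muscle and side is tested separately, and activation is defined as a sequence, so eight separate rank tests are one reading of it. The definitions make the outcomes dependent. Some differences are also likely to be real: slow walking is one of the Fried criteria, the signals are recorded during self-paced walking, and IEMG accumulates over time. Each real difference leaves fewer nulls to go wrong.

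A reader might also infer that a missing adjustment method is itself the error. Such methods are commonly left to a statistical analysis plan, which may exist unseen. The study is observational, sets out to characterise sEMG signals, and describes the predictive work as exploration.

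These arguments reduce the size of the problem but do not remove it. The article itself fixes the unranked primary list, the single significance level and the one unattributed effect size. A later plan would have to change those statements, not merely fill them in.

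**Conclusion.** The point stands in measured form. The primary family has no hierarchy, and its family-wise error rate is not held at 5%. Under no true difference and independence it is 34% to 95% across the plausible counts of 8 to 60. For 60 tests with assumed strong correlation it is roughly 40-87%, and about 20% at the extreme of 0.9 among all tests, which is still four times the nominal level. The count, the correlations and the all-null condition are assumptions. The expected 3.0 false positives from 60 tests depend on the count and the all-null condition, but not on correlation.

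The 80% power statement does not describe this family. Even for one parameter with d = 0.433, it holds at 67 per group only for a one-sided test. Under the two-sided rule, power is about 70% at 67 and 75% at 75 per group.

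**What to change.** Before the data are analysed, and without reference to group results:
- Name one primary parameter and one muscle. Use the source of 0.433 if that figure belongs to a single parameter; if it does not, say how it was obtained and on what grounds the primary was chosen. Test it at two-sided 0.05.
- Reclassify all other sEMG parameters as secondary. Report them with Benjamini-Hochberg control at 5% across that family, showing raw and adjusted P values.
- State that the power statement applies only to the named parameter, and restate it for the two-sided test: about 70% at 67 and 75% at 75 per group, if d = 0.433 is the effect assumed for that parameter.

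The cost is a change of wording and one adjustment step, with no new data. The downside is that fewer secondary parameters will be called significant and the stated power will be less favourable.

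### The symmetry index keeps its left-minus-right sign, so the group test measures laterality, and asymmetries on opposite sides cancel instead of showing as greater asymmetry in frailty

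*Protocol article*

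**What the plan says.** Under Outcome measures and calculation algorithms, Primary outcome, item (3), the protocol article sets SI equal to left RMS minus right RMS, divided by their sum. The sign is kept and interpreted: "A result greater than 0 will indicate that the discharge from the muscles on the left side is greater than that on the right"; a negative value means the reverse.

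The opening of the same section makes SI part of the primary outcome, which covers the time- and frequency-domain indicators "along with the symmetry index (SI), muscle activation sequences, and muscle contribution ratios derived from these indicators". The abstract also lists it there.

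The Statistical analysis section has one rule for all measurement data. If normally distributed, they are summarised by mean and SD, "with comparisons between groups made using the two independent samples t-test". Otherwise "comparisons between groups will be conducted using the Mann-Whitney U test". Parameters associated with frailty then go from correlation to logistic regression, and those significant there go on to ROC curves.

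The article contains no absolute value, no dominant/non-dominant coding and no stronger/weaker-side coding. Nor does it state that frailty is expected to affect one particular leg. The primary objective concerns four muscles in both legs.

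**The concern.** Both planned tests respond to a shift in location. Applied to signed SI, they ask whether frail participants are, as a group, more left-active than controls. An outcome called a symmetry index would normally be expected to answer a different question: whether the two legs differ more in frail people than in controls.

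If some frail participants discharge more on the left and others more on the right, positive and negative values offset each other. The group mean or median then sits near 0, as it does in controls. A named primary outcome would return no difference even where asymmetry is marked, and that could be reported as preserved symmetry in frailty.

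The fault carries forward. A parameter that fails the correlation screen is not entered in the logistic model or the ROC analysis, so an informative marker could be lost to the secondary objective on diagnostic value.

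**Working it through.** **Inputs from the protocol article.** SI = (L − R)/(L + R); t-test or Mann-Whitney U; two-sided 0.05; 1:1 groups; 67 evaluable per group.

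The 67 reproduces from the stated effect size of 0.433 and 80% power when alpha of 0.05 is one-sided: 66.6, rounded up to 67, and 67/0.9 = 74.4, rounded up to 75. With two-sided alpha the answer is 84.7, that is 85. That mismatch is a separate matter; 67 is used here only as the evaluable number.

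**Assumed, because the article gives no SI data.** Control SI is normal with mean 0 and SD 0.10. Frail participants either have a wider spread around 0 (k times the control SD), or are shifted by +m or −m with SD 0.10, a share p being left-dominant.

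**Step 1: the mean.** The frail group's mean signed SI is p·m − (1 − p)·m = m(2p − 1). At p = 0.5 this is 0 for every m. With m = 0.10 and p = 0.5, the simulated mean signed SI was 0.000, while mean |SI| was 0.117 in frail participants and 0.080 in controls. The difference exists and the sign removes it.

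**Step 2: the ranks.** With an even split both distributions are symmetric about 0, so the probability that a frail value exceeds a control value is 0.5. Mann-Whitney U therefore has nothing to detect either.

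**Step 3: rejection rates.** 10,000 simulated studies per row, 67 per group, two-sided 0.05, even left/right split.

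| Frail group | Signed, t | Signed, M-W | Unsigned, t | Unsigned, M-W |
|---|---|---|---|---|
| Spread k = 1.25 | 5.2% | 5.2% | 38.7% | 29.0% |
| Spread k = 1.5 | 5.6% | 5.7% | 85.8% | 72.2% |
| Spread k = 2 | 5.5% | 6.0% | 99.9% | 98.9% |
| Shift m = 0.05 | 5.1% | 4.9% | 13.8% | 11.7% |
| Shift m = 0.10 | 5.2% | 5.3% | 85.0% | 78.2% |
| Shift m = 0.15 | 4.8% | 5.9% | 100% | 100% |
| Shift m = 0.20 | 5.5% | 7.9% | 100% | 100% |

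In the spread rows only the ratio k matters, so the assumed SD of 0.10 does not affect them. In the shift rows the ratio of m to the SD matters.

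**Step 4: uneven sides.** With m = 0.10, the signed t-test rejects in 16.0% of studies at p = 0.6, 49.2% at p = 0.7, 84.0% at p = 0.8 and 100% at p = 1.0. The t-test on |SI| stays at 85% to 86% throughout.

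**Step 5: later analyses.** With m = 0.20 and an even split, the AUC is 0.50 for signed SI by symmetry. For |SI| it is Φ(√2)² + (1 − Φ(√2))² = 0.9214² + 0.0786² = 0.855; simulation gave 0.86.

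**The case against.** The strongest reply is that the article never says SI is meant to show greater asymmetry. It gives the sign a meaning, and a signed index is a valid measure of which side is more active. That is true, and signed SI has a place as description. But no lateralised hypothesis is stated, and an outcome named for symmetry will be read as a statement about symmetry.

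Second, the loss of power is complete only when the sides balance, and the article gives no side distribution. This also stands. If one side predominates, the signed test gains power and can exceed |SI|: at m = 0.05 and p = 0.8 the t-test rejects in 38.3% of studies with signed SI, against 14.8% with |SI|. What it then detects is laterality, not the amount of asymmetry.

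Third, |SI| does not rescue small effects: 11.7% to 13.8% at m = 0.05, and 29.0% to 38.7% at k = 1.25. The change makes the test answer the right question. It does not guarantee adequate power.

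Fourth, SI is one of several primary parameters. RMS, IEMG, AEMG, MPF and MF do not depend on it, and a wider spread in the frail group would show in the reported SD or IQR. The damage is confined to SI, but a visible, untested spread does not replace a test on a primary outcome.

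**Conclusion.** The concern holds. As written, the group comparison of SI tests left-right laterality. When left- and right-dominant participants are balanced, signed SI rejects at about the nominal 5% (4.8% to 6.0% in most scenarios, at most 7.9%) whatever the degree of asymmetry. For a spread ratio of 1.5 or a random-side shift of 0.10, the same data analysed as |SI| would give 72% to 86%.

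The cancellation follows from the formula and the two tests and needs no assumption about the SD. The power figures rest on assumed normal distributions, controls centred at 0, and assumed spreads and shifts, and should be read as illustrations. The practical conclusion is that a null SI result could not support a claim that symmetry is unaffected by frailty.

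**What to change.** - Define the between-group symmetry outcome as |SI| = |L − R|/(L + R) for each muscle, and keep signed SI as a descriptive column for direction.
- State the order of operations. Because three walks are averaged, average first and take the absolute value last; taking it within each walk would let walk-to-walk noise inflate |SI|.
- Name one test in advance. Mann-Whitney U suits a bounded, right-skewed measure. The t-test had somewhat more power in the scenarios above, so the choice should not wait for the data.
- Use |SI| in the correlation, logistic and ROC steps as well.
- If laterality really is of interest, state that hypothesis separately and keep a signed or dominant-side comparison for it.

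The cost is a few lines of text and no new data. Since recruitment and data collection were already under way when the article was submitted, the change to a primary outcome should be made as a dated amendment, with the registration updated, before analysis begins.

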### Test program

(1)Instrument preparation and electrode placement: Surface EMG signals will be collected using the Dinuo Surface EMG Analyzer and Feedback Instrument (Zhejiang Dinuo Medical Science and Technology Co., Ltd., model SG-800A). Before testing, the instrument is adjusted and set to a sampling frequency of 2000 Hz. This wireless EMG testing method, in contrast to wired electrodes, offers greater convenience and less interference with actions, suitable for a broader range of application scenarios. Participants will be required to expose the skin of their lower limbs, depilate any excessive hair on the muscle surface, and disinfect and degrease the designated testing area using a 75% alcohol cotton ball. Electrodes are placed once the skin has dried to minimize impedance. Placement of all recording electrodes adheres to the European recommendations of the Surface ElectroMyoGraphy for the Non-Invasive Assessment of Muscles (SENIAM). Single-use EMG recording electrode patches (Zhejiang Dinuo Medical Technology Co., Ltd., model E5) are affixed to the rectus femoris (midpoint between the anterior superior iliac spine and the patella’s upper edge), semitendinosus (midpoint between the ischial tuberosity and the tibia’s medial epicondyle), tibialis anterior (one-third along the line from the fibula’s tip to the inner ankle’s tip), and medial head of the gastrocnemius (muscle’s most prominent bulge). Electrodes are placed on the muscle belly’s most prominent part, parallel to the muscle fibers. A reference electrode patch is placed on a non-tested muscle to avoid test interference. Electrodes are secured with elastic bandages to prevent displacement and movement during the walk, thereby reducing motion artifacts. The illustration of electrode placement and bandage fixation is shown in Fig 2.

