**Fig 2 pone.0325356.g002:**
[figure not shown]
Figure of electrode placement and bandage fixation for surface electromyography recording.

(2)10-meter walk test: A 12-meter stretch will be marked on an open and flat 15-meter walkway, incorporating a 10-meter timed section flanked by 1-meter zones for acceleration and deceleration at both ends. After the surface EMG recording and reference electrodes have been properly placed, subjects will be instructed to stand still and relaxed at the starting line, with the aim of maintaining the EMG signal near the baseline (<10 μV) as displayed on the instrument. Upon the ‘start’ signal, participants will walk to the finish line at a comfortable pace, maintaining a natural walking speed. The time taken to traverse the 10-meter timed section will be recorded using a timer, and dynamic sEMG parameters of the lower limb muscles will be captured by the surface EMG device, complemented by recordings of different gait cycles using an infrared camera system for further analysis. Typically, three tests will be conducted with 1–2 minutes of rest between each, and the average result of these three tests will be calculated. The entire test will require the accompaniment of a researcher to ensure safety, without any physical contact, and no assistive devices will be used by the subjects during the test.

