### Data processing

Surface EMG data analysis will be performed using the proprietary wireless surface EMG analysis feedback software (Zhejiang Dino Medical Technology Co., Ltd.). Data from five gait cycles following the third cycle (i.e., the 4th to 8th gait cycles) will be analyzed. First, the surface EMG signals will be band-pass filtered using a zero-delay Butterworth filter between 20 and 500 Hz to remove noise and irrelevant frequencies from the signals. Afterward, adaptive filtering will be applied to eliminate ECG interference. Once filtering is complete, an analyst will visually inspect the raw EMG data to identify any motion artifacts or noise. The EMG signals will then be rectified and smoothed (using averaging) to convert negative values into positive ones and ensure signal smoothing. However, smoothing filters will not be applied for frequency-domain analysis. To reduce inter-individual variability, the maximum value of the rectified EMG signals (EMG_max) will serve as a benchmark for normalization. Finally, the rectified EMG signals from the 5 gait cycles will be normalized to EMG_max, meaning that all EMG values will be expressed as a ratio relative to EMG_max.

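### The muscle-onset rule does not fit the restriction to gait cycles 4 to 8, so the activation-sequence outcome is either cut-dependent or describes gait initiation

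*Protocol article*

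**What the plan says.** Under Primary outcome, item (4), the protocol article gives a complete detection rule. Onset is the point at which the following holds: "When the average of 10 consecutive sampling points of the EMG signal first exceeds the baseline value". The threshold, which the article calls the baseline, is "1.7 times the maximum value of the first 20 sampling points". Muscles are then ranked by onset time. The same section lists activation sequence among the primary outcomes.

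Three other statements bear on the rule:

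- Test program, item (1): the instrument is "set to a sampling frequency of 2000 Hz".
- Test program, item (2): before the start signal, "subjects will be instructed to stand still and relaxed at the starting line", with the aim of keeping the displayed signal below 10 μV. An infrared camera records the gait cycles.
- Data processing: "Data from five gait cycles following the third cycle (i.e., the 4th to 8th gait cycles) will be analyzed". The signal is "band-pass filtered using a zero-delay Butterworth filter between 20 and 500 Hz", then rectified and smoothed by averaging over a window whose length is not given.

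Item (4) does not say whether the first 20 points are the first of the recording or the first of the analysed cycles. Nor does it say what happens to a muscle that never crosses.

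**The concern.** An onset threshold is meaningful only if it is taken while the muscle is at rest, and only if the crossing it detects lies in the movement under study. The rule as written does not secure both at once. Mid-walk, nothing ensures that each muscle is at rest in the opening 10 ms. At the start line the muscles are at rest, but the first crossing after that is the first step.

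The stake is one named primary outcome. If the threshold is taken mid-walk, a muscle's rank reflects which muscles happen to be active where the segment begins. A difference between frail and non-frail participants in phase at the cut could then look like a difference in sequence, and a real difference could be lost. Parameters found significant go on to the logistic regression and ROC steps in Statistical analysis, so an artefact could be carried forward.

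**Working it through.** **Inputs from the protocol article.** Sampling 2000 Hz; threshold 1.7 × maximum of the first 20 samples; detection on the mean of 10 samples; filter band 20-500 Hz; analysis of cycles 4 to 8; four muscles in each of two legs, so eight in all. The article gives no error rate for the rule, so there is no stated figure to reproduce.

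**Time scale.** Baseline length = 20 / 2000 s = 10 ms. Detection window = 10 / 2000 s = 5 ms. The lower filter edge has a period of 1/20 s = 50 ms, so the baseline covers one fifth of it. With a bandwidth of 480 Hz, it holds about 2 × 480 × 0.010 ≈ 10 independent values.

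**Assumptions not in the documents.** EMG modelled as Gaussian noise band-passed at 20-500 Hz and rectified; moving-average smoothing of 0, 10, 50 or 100 ms; active-to-rest amplitude ratio 5 or 10 (3 also tried); 1.1 s cycle with a burst for 40% of it; 2 s of quiet standing. There were 400 runs per setting, and 600 for rest only.

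**Results.** Paired figures are for ratios 5 and 10.

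| Smoothing | Active when cycle 4 opens: no onset | Active: correct within 50 ms | Quiet when cycle 4 opens: correct within 50 ms | Standing baseline: start of activity within 50 ms | False onset in 2 s of rest |
|---|---|---|---|---|---|
| none | 98.0%, 97.5% | 0.3%, 0% | 99.0%, 99.0% | 98.5%, 98.5% | 2.2% |
| 10 ms | 80.2%, 80.0% | 0.5%, 1.0% | 88.2%, 90.5% | 77.5%, 77.0% | 25.3% |
| 50 ms | 99.8%, 99.3% | 0%, 0% | 100%, 100% | 99.8%, 99.5% | 0.2% |
| 100 ms | 100%, 100% | 0%, 0% | 100%, 100% | 100%, 99.8% | 0% |

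The Monte Carlo error near 80% is about 1.96 × √(0.8 × 0.2 / 400) ≈ 4 percentage points. A repeat with fresh draws put the lowest no-onset figure at 75%, hence the range of about 75-100%. Smoothing lengths not tried could fall somewhat outside it. At ratio 3 without smoothing, the standing baseline placed the start of activity within 50 ms in about 70% of runs and missed it in about 5%.

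**Possible readings of the rule, set against cycles 4 to 8.**

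1. *Points open the analysed segment.* Muscles quiet at that instant are timed well; muscles already active are almost never timed correctly.
2. *Points open the recording, search from there.* Timing is usually good, but the event is gait initiation, before cycle 4.
3. *Standing threshold, search starting at cycle 4.* Every muscle active at the opening crosses at once, so these muscles tie at time zero.
4. *Restart at each cycle.* This repeats the fault of reading 1 at every cut.

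Readings 1, 3 and 4 give a steady-state order only if all ranked muscles are quiet at the cut. As an illustration, if each of eight muscles were active 20-40% of the time independently, the chance of this would be 0.8⁸ ≈ 17% down to 0.6⁸ ≈ 2%. Real timings are correlated, so these are not estimates for this study.

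**What does not rescue the rule.** Dividing by EMG_max scales signal and threshold alike. Averaging three walks does not remove a systematic error.

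**The case against.** The strongest reply is that the quiet-standing reading is the natural one. The article uses the word baseline for relaxed standing in Test program, item (2), and again for the threshold. It also ties contribution rate, item (5), expressly to the five analysed cycles but does not do so for item (4). From a quiet start the rule mostly works, so the sequence is neither undetectable nor badly computed. A condensed article may also leave per-cycle application to the full protocol or the software.

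Much of this stands. A reader might infer that 10 ms of baseline makes the sequence wrong or undetectable on any reading. The article and the simulation do not support that: a standing baseline, or a muscle quiet when cycle 4 opens, usually gives good timing. A reader might also infer that short, fragmented offsets damage the outcome, but the ranking uses onset times only. Nor should one quote a fixed rate at which the wrong muscle is ranked first, because that depends on how many muscles are assumed active at the cut, and the article gives no activity timing.

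What the reply does not remove is the mismatch. If the standing reading is right, the sequence describes the first step while Data processing analyses cycles 4 to 8. The article states a definite rule with a single first crossing, so this is a conflict between two stated rules and not merely omitted detail.

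**Conclusion.** The concern holds in this form: the onset rule and the restriction to cycles 4 to 8 do not fit together. With the threshold taken at the opening of the analysed segment, a muscle already active there has no onset in about 75-100% of simulated recordings, and its rank depends on the cut. With the threshold taken in quiet standing, the rule usually detects the start of activity, but of gait initiation.

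The percentages rest on assumed burst patterns, amplitude ratios and smoothing lengths. The conflict between the two sections does not. The 10 ms baseline is secondary: with a quiet start it adds false onsets in under 1% to about 25% of 2 s rest periods, depending on the unstated smoothing length. Only the activation sequence is affected; RMS, IEMG, AEMG, MPF, MF, the symmetry index and contribution rate do not use the onset rule.

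**What to change.** Re-specify item (4) before the data are analysed:

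- Take the baseline from a defined quiet-standing segment before the start signal, much longer than 10 ms (for example 500 ms or more), with the threshold set from its mean and SD.
- Detect the off-to-on crossing within each of cycles 4 to 8, with a minimum duration above threshold.
- Time each onset relative to a gait event from the camera recording, and average over cycles before ranking.
- State the smoothing length and how a muscle with no crossing is handled.

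The numerical settings are examples; what matters is that they are fixed in advance. The cost is reprocessing work. The sponsor must first confirm that the standing signal is stored and that the raw signal can be exported from the proprietary software, since the article states neither.
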